### Participants

Sixty comorbid alcohol dependent and depressed patients, 30 alcohol dependent only and 30 depressed only patients will be included for T1 assessment. Further, 30 healthy control participants (matched according to age, gender and educational level) will be recruited.

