### Sample recruitment

Participants of the study are recruited by means of several sources in the community around Mannheim, Germany. These include advertisement in local newspapers, announcements on our institutes’ homepage, flyers in local businesses and university campuses; and contact with potential referral sources, for example general practitioners, private psychologists and psychiatrists, as well as local psychiatric inpatient and outpatient units.

Prospective participants express their interest to the research team through email or phone call. After carefully informing the participants about the aim, content, duration and potential risks and benefits of the study, trained research assistants assess initial eligibility using a specifically developed telephone screening. In case the participants are currently in one of the local inpatient or outpatient facilities of the institute, participants will be personally approached and screened. If the individual meets the inclusion criteria, they receive a letter including a detailed study description, the informed consent, time and date of their study appointment and an online link with questionnaires.

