### Randomization

After completion of baseline assessment, comorbid patients will be randomly assigned to one of the two group interventions. To reduce the time between the initial study recruitment and the start of the group therapy, the randomization order will be determined with a block randomization with 6 participants per block for each treatment arm. Randomization will be performed by a researcher who is not involved in the recruitment, using a computerized randomization tool implemented in MATLAB (The MathWorks Inc., Natick, Massachusetts, United States). Participants will be recruited and enrolled by trained research staff; the allocation sequence will be concealed from them. Since the study offers psychotherapeutic interventions, patients are not blinded to their intervention arms.

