### Psychotherapeutic Interventions

Comorbid patients will be randomly assigned to one of two group therapies consisting of 6 participants. Both interventions consist of six sessions of 2 h therapy with 1 session per week offered by a psychotherapist. To increase adherence, ﻿each participant will receive an individual therapy session before the group therapy begins. The group therapy protocols in both arms are manualized and supervised by an experienced psychotherapist to ensure protocol adherence. Patients who missed more than one session or experienced a severe relapse during the intervention period will be excluded from the protocol. In the unexpected case of an adverse event or harm during the psychotherapeutic intervention (for example, severe aggravation like suicidality), the affected patient will also be excluded and additional in- or outpatient treatment will be offered by the psychotherapist.

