### Behavioral data analyses

Analysis will be completed by using (repeated measures) analysis of variance (AN(C)OVA) in order to test group differences (AUD vs MD vs Co vs HC) and treatment groups (BAT vs MBT). Difference scores will be calculated. All measures will be compared between groups, as well as treatment groups and interaction effects will be explored. Wherever appropriate, missing data will be imputed using multiple imputation.

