One limitation of the study might concern the lack of a proper control group for the investigation of the treatment effects (for example waiting control group). However, this study was not designed to evaluate treatment effects per se but rather to investigate the neurobiological correlates of established psychotherapeutic interventions. With this, we are specifically interested if the targeted interventions positively alter the pathophysiology of comorbid patients and whether this is restricted to patients with a specific neurobiological signature. A second challenge affects the recruitment of comorbid depressed and alcohol dependent patients. Not only for the fMRI measurement, but also for the feasibility of the group therapy patients abstinence is a prerequisite. In order to motivate comorbid patients to participate in the group therapy and to stay abstinent, we want to guarantee a fast study enrolment, as well as ensure a short latency between study enrolment and begin of group therapy. For that reason, we decided for a group randomization of 6 participants per block. With this, we might risk recruitment-dependent biases. However, due to many different recruitment strategies and sources, we hope to reduce this potential bias to a minimum.

To reach the project results is one of the key issues and core challenges to contribute to a better neurobiological understanding and treatment of comorbid depression and alcohol dependence. The project will help to improve knowledge on pathophysiology, identify targets for treatment development, detect subgroups for treatment selection, and facilitate the use of neurobiology findings in the understanding of comorbid alcohol dependence and depression.

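### With groups of six allocated together, the number of recruitment sources cannot be relied on to balance the BAT and MBT arms

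*Protocol article*

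**What the plan says.** The Participants section of the protocol article fixes the randomised population: "Sixty comorbid alcohol dependent and depressed patients, 30 alcohol dependent only and 30 depressed only patients will be included for T1 assessment". Only the 60 comorbid patients are randomised, to BAT or MBT.

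Three places describe the allocation unit:

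- Randomization: "the randomization order will be determined with a block randomization with 6 participants per block for each treatment arm".
- Psychotherapeutic Interventions: "Comorbid patients will be randomly assigned to one of two group therapies consisting of 6 participants".
- Discussion, where the stated motive is a short wait before therapy: "For that reason, we decided for a group randomization of 6 participants per block".

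The Discussion then admits a possible recruitment-dependent bias and gives one countermeasure: "due to many different recruitment strategies and sources, we hope to reduce this potential bias to a minimum".

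The Sample recruitment section lists newspaper advertisements, the institute's homepage, flyers, practitioner referrals and local psychiatric units. Patients already in one of the institute's own facilities follow a different route: they "participants will be personally approached and screened".

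Under Behavioral data analyses, (repeated measures) AN(C)OVA is used to "test group differences (AUD vs MD vs Co vs HC) and treatment groups (BAT vs MBT"). No covariate or block term is named.

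**The concern.** The number of sources is not a balancing mechanism. With a single source the arms could not differ in source at all; a difference becomes possible only when there are several. If six patients go to one arm together and a block happens to be filled largely from one ward or one advertising campaign, that source mix passes whole into one arm. With about five blocks per arm there is little averaging.

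At stake is the only randomised comparison in the study. If inpatients and community patients differ in expected T1-T2 change, a source imbalance shifts the BAT-MBT contrast. There is no untreated arm in which such a shift could be recognised, as the Discussion itself acknowledges.

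**Working it through.** The plan gives no figure for this point, so there is nothing to reproduce. The check asks how much source imbalance group allocation allows, and what it does to the test.

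**Inputs from the article.** 60 randomised patients; groups of 6; two arms. Hence 60/6 = 10 units, about 5 per arm, 30 patients per arm.

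**Assumptions, none of them in the article.** Half the patients are inpatients (p = 0.5). The intra-block correlation of source, ICC, is 0 to 0.75. Source shifts the change score by δ = 0.2 to 0.8 within-source SD. Groups of six go to one arm as a unit.

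**Step 1: imbalance in source share.** Design effect DE = 1 + (6 − 1) × ICC. SD of the arm difference = √(0.25 × DE × 2/30). At ICC 0 this is √(0.25 × 1 × 2/30) = 0.129; at ICC 0.5 it is √(0.25 × 3.5 × 2/30) = 0.242. The last column comes from beta-binomial simulation of 10 blocks of six.

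| ICC | DE | SD of arm difference | P(difference ≥ 20 points) |
|---|---|---|---|
| 0 | 1.00 | 0.129 | 15% |
| 0.1 | 1.50 | 0.158 | 25% |
| 0.25 | 2.25 | 0.194 | 35% |
| 0.5 | 3.50 | 0.242 | 45% |
| 0.75 | 4.75 | 0.281 | 52% |

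Individual 30:30 allocation of the same 60 patients gives 15-17% whatever the ICC.

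**Step 2: does adding sources help?** With single-source blocks, the mean total-variation distance between the arms' source distributions is 0.25 for 2 sources, 0.34 for 3 and 0.52 for 6. With sources mixed within blocks it is 0.10, 0.15 and 0.23. At a given number of sources, mixing reduces the imbalance; raising the number does not.

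**Step 3: effect on the test.** A 20-point imbalance shifts the arm contrast by 0.20 × δ: 0.20 × 0.5 = 0.10 SD, or 0.20 × 0.8 = 0.16 SD. Over repeated trials, the intra-block correlation that source induces in the outcome is ρ = ICC × 0.25δ² / (1 + 0.25δ²). The type I error of a test that ignores blocks is approximately 2 × [1 − Φ(1.96/√(1 + 5ρ))].

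Worked case, ICC 0.75 and δ = 0.8: 0.25 × 0.64 = 0.16; ρ = 0.75 × 0.16/1.16 = 0.103; 1 + 5 × 0.103 = 1.517; 1.96/√1.517 = 1.59; two-sided error 11.2%. Simulation gives 11.5-12.1%.

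| ICC | δ = 0.2 | δ = 0.5 | δ = 0.8 |
|---|---|---|---|
| 0 | 5.0% | 5.0% | 5.0% |
| 0.1 | 5.1% | 5.3% | 5.8% |
| 0.25 | 5.1% | 5.9% | 7.0% |
| 0.5 | 5.3% | 6.7% | 9.1% |
| 0.75 | 5.4% | 7.6% | 11.2% |

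These are formula values; simulation agrees to within about one percentage point.

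**Step 4: what restores the error rate.** In simulation, an individual-level model with source as covariate gives about 5% (4.7-5.5%). A test on block means without any source covariate also gives about 5% (4.9-5.1%). The mean arm difference over repeated trials is about zero.

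**The case against.** The strongest reply has five parts.

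- **The text is a disclosure.** The Discussion names the risk as a limitation and expresses a hope. That is fair, and it should not be read as a firm claim of protection. It is still the only countermeasure offered.
- **Parallel sources may mix.** The channels listed could well run at the same time, and at ICC 0 group allocation is no worse than individual allocation. This stands: the number of sources cannot be relied on, but it is not shown to fail.
- **The inflated error is a clustering problem.** This also stands. A block-level analysis removes it without any source covariate. What the covariate adds is correction of an imbalance actually observed in this one trial; a block term widens the error but does not remove that shift.
- **Stable differences cancel.** Severity differences that do not change from T1 to T2 drop out of difference scores and of the group-by-time interaction, and the abstinence requirement narrows the contrast. Only a source difference in expected change matters, and its size is assumed here.
- **The study was not designed to evaluate treatment effects as such.** True, but the article still plans and powers a group-by-time comparison of BAT with MBT.

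A reader might infer that the absence of recruitment source from Table 1 and from the analysis section is itself an error. It is not. A condensed article commonly leaves screening fields and covariate lists to the full protocol or analysis plan; AN(C)OVA leaves room for covariates; and previous therapy, medication and health care use are collected at T1. A reader might also infer systematic bias. The blocks are randomised and the sequence is concealed from recruiting staff, so the documents support only excess chance imbalance.

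**Conclusion.** The point holds in a limited form. Across about 10 allocation units, the number of recruitment sources does not control imbalance between BAT and MBT; only mixing within blocks does, and no section provides for it. The chance of a 20-point difference in source share is about 15% with full mixing and about 52% at an intra-block correlation of 0.75. The type I error of an individual-level test is about 5% when the correlation is near zero or the source effect is small, and about 12% at the far end of the assumed range.

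All of this rests on the assumed 50% inpatient share, correlation and effect size, and on reading the allocation unit as a whole group of six. The Discussion and the Psychotherapeutic Interventions section support that reading. The Randomization section alone could be taken as ordinary permuted blocks, although that would not explain the risk that the Discussion concedes. That the six are consecutive enrolees is an inference. Severity is minor to moderate.

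**What to change.** 1. Record the recruitment source of each comorbid patient at screening: inpatient, outpatient or referral, community.
2. Show source by arm and by block.
3. Include source as a prespecified covariate in the BAT-MBT models, behavioral and fMRI, alongside and not instead of a therapy-group or block term.
4. Reword the Discussion sentence so that the number of sources is not given as the protection; point instead to the recording, display and adjustment.
5. State the allocation unit in the same words in the Randomization section and the Discussion.

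The cost is one screening field, which staff already know at first contact, and one or two degrees of freedom. Group formation and waiting time stay as they are.

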## Abbreviations

AUD: Alcohol Use Disorder
BAT: Behavioral Activation Training
Co: Comorbid patients
DMN: Default mode network
fMRI: Functional magnetic resonance imaging
HC: Healthy controls
MBT: Minfulness based training
MD: Major depression
NAc: Nucleus Accumbens
PFC: Prefrontal Cortex
VS: Ventral Striatum
